## Abstract

**Background:**

Most breast cancer patients undergoing mastectomy are candidates for breast reconstruction. Deciding about breast reconstruction is complex and the preference-sensitive nature of this decision requires an approach of shared decision making between patient and doctor. Women considering breast reconstruction have expressed a need for decision support. We developed an online patient decision aid (pDA) to support decision making in women considering immediate breast reconstruction. The primary aim of this study is to assess the impact of the pDA in reducing decisional conflict, and more generally, on the decision-making process and the decision quality. Additionally, we will investigate the pDA’s impact on health outcomes, explore predictors, and assess its cost-effectiveness.

**Methods:**

A multicenter, two-armed randomized controlled trial (1:1) will be conducted. Women with breast cancer or ductal carcinoma in situ who will undergo a mastectomy and are eligible for immediate breast reconstruction will be invited to participate. The intervention group will receive access to the online pDA, whereas the control group will receive a widely available free information leaflet on breast reconstruction. Participants will complete online questionnaires at: baseline (T0), 1 week after consultation with a plastic surgeon (T1), and 3 (T2) and 12 months (T3) after surgery. The primary outcome is decisional conflict. Secondary outcomes include other measures reflecting the decision-making process and decision quality (e.g., decision regret), patient-reported health outcomes (e.g., satisfaction with the breasts) and costs.

**Discussion:**

This study will provide evidence about the impact of an online pDA for women who will undergo mastectomy and are deciding about breast reconstruction. It will contribute to the knowledge on how to optimally support women in making this difficult decision.

**Trial registration:**

This study is retrospectively registered at ClinicalTrials.gov (NCT03791138).

## Background

Breast cancer is the most prevalent type of cancer amongst women [1, 2]. In Western European countries, approximately one in eight women will develop breast cancer over the course of her lifetime [1, 3]. In The Netherlands alone, more than 14 000 women developed breast cancer in 2018 [1]. Approximately 60–70% of all breast cancer patients undergo breast-conserving surgery (BCS) in which the tumor and a margin of surrounding breast tissue is removed, conserving breast shape as much as possible [4–6]. However, another 30–40% of breast cancer patients undergo a mastectomy, in which all breast tissue is removed and breast contour therefore is lost [4–7]. Breast cancer surgery, especially mastectomy, can negatively impact psychosocial outcomes such as body image, sexual functioning and health-related quality of life [8–11]. To restore breast contour, and potentially reduce the negative psychosocial impact of mastectomy, women may opt for breast reconstructive surgery.

Breast reconstruction can be performed immediate at the time of mastectomy, or delayed, typically when treatment for breast cancer is completed. Furthermore, there are several types of breast reconstruction (implant-based, autologous, and a combination of both). All options have their pros and cons, and personal values and preferences of women play an important role in this decision [12, 13]. In the last decades, the number of women choosing breast reconstruction, and especially immediate breast reconstruction, has increased substantially [14–16].

Decision making regarding breast reconstruction is complex and can be challenging for women. Women often have to consider multiple options within a short and stressful period following breast cancer diagnosis, and make a decision in this timeframe that will have a lasting impact on the rest of their lives. Previous studies have highlighted the importance of the provision of high-quality, realistic preoperative information and decisional support to enable women to make a long-term satisfying decision about breast reconstruction [17–24]. Although most women are satisfied with their reconstructed breast, and decision regret is generally low [25], a minority of women experience mild to moderate levels of regret [17, 26]. Both knowledge of breast reconstruction and decisional preparedness have been shown to be low among women deciding about breast reconstruction [27–29]. A single-centre, cross-sectional study among 126 women undergoing mastectomy demonstrated that less than half of the participants made a high-quality decision regarding breast reconstruction, defined as having knowledge of important breast reconstruction facts and undergoing treatment in accordance with one’s personal preferences [30].

Patient decision aids (pDAs) are tools developed to support shared decision making between patients and physicians [31]. PDAs explicitly state the treatment decision that patients face, consist of evidence-based information about treatment options including their pros and cons, and clarify personal values relevant for the decision [31]. Across a wide variety of treatment decisions, pDAs have been found to reduce decisional conflict, increase knowledge and increase insight into personal values related to the decision, without increasing anxiety [32, 33].

Worldwide, only a limited number of interventions to support patient decision making about breast reconstruction are available [34]. In a recent review assessing the effectiveness of these interventions as compared to a control group, eight studies on seven distinct interventions were identified [34]. While the intervention improved patient satisfaction and involvement in decision making in all studies that reported on that specific outcome, results on other important outcomes were mixed [34]. In three out of five studies the intervention reduced decisional conflict [35–37], in two out of three studies the intervention reduced regret [35, 38] and in one out of three studies the intervention improved knowledge [39]. Furthermore, most included studies were rated as of weak methodological quality and none were undertaken in a European country.

To support women in making an informed decision regarding immediate breast reconstruction following mastectomy, we developed an online pDA for the Dutch population. The aim of this study is threefold. First, we aim to investigate the impact of this pDA on the decision-making process (in terms of decisional conflict, satisfaction with information, satisfaction with plastic surgeon, preparedness for decision making, perceived shared decision making, and involvement in decision making), on decision quality (in terms of knowledge of breast reconstruction and decision regret), and on patient-reported health outcomes (in terms of actual choice, satisfaction with breast, body image, sexual functioning, anxiety, and breast symptoms). Second, we aim to explore factors that are predictive of the effectiveness of the pDA. And third, the cost-effectiveness will be investigated.

## Methods/Design

### Design

We will conduct a multicenter, two-armed randomized (1:1) controlled trial. The trial protocol was retrospectively registered at the 1st of January 2019 in ClinicalTrials.gov (NCT03791138).

### Study setting

The study will be conducted in eight hospitals (two academic centres, five general hospitals and one cancer-specialized hospital) throughout the Netherlands.

### Eligibility criteria

The study sample will be composed of women (≥18 years of age or older) diagnosed with breast cancer or ductal carcinoma in situ, who will undergo mastectomy, are eligible for immediate breast reconstruction and have been referred to a plastic surgeon. The consultation with a plastic surgeon should be scheduled at least three working days after study invitation, to allow participants for sufficient time to complete informed consent (IC) and the baseline questionnaire and use the pDA or information leaflet prior to their consultation. Additionally, women must have internet access, basic computer skills and sufficient command of the Dutch language.

### Procedure

Prior to study commencement, all members of the surgical breast cancer team will receive access to the pDA and attend a meeting to familiarise with the pDA and study procedures. No further training on the delivery or use of the pDA is provided.

Women will be invited for study participation by their treating surgical oncologist, nurse specialist or breast cancer nurse during a regular pre-surgical treatment consultation in which the possibility of breast reconstruction is also discussed. The clinician will provide patients with a study information package consisting of a patient information letter and a sheet outlining patient’s treatment options that allows women to tailor the pDA to their situation (see Intervention). Patients will give written approval for sharing their contact information with the research team. A member of the research team will then contact the patient by phone to give detailed study information and to check whether inclusion criteria are met. Eligible women who are interested in participating will receive two emails, one with a link to the online IC form and one with a link to the baseline questionnaire (T0). Following completion of both, participants will be randomly allocated to the intervention or control group. Women in the intervention group will receive access to the online pDA. They will receive an email with a link to the pDA and a personal login code. Women in the control group will receive an email with a digital version of a widely available free information leaflet on breast reconstruction. Two days prior to consultation with their plastic surgeon, participants in the intervention group and the control group will be reminded by email about the possibility of using the pDA or the information leaflet respectively. Study allocation will be noted in patients’ medical records, allowing plastic surgeons to discuss the summary sheet of the pDA (see Intervention) with patients in the intervention group. Participants will complete questionnaires at T1 (1 week after consultation with the plastic surgeon), T2 (3 months after breast surgery) and T3 (12 months after breast surgery). Questionnaires will be completed online and will be available in paper format upon patient request. To minimize missing data in online questionnaires, we will mark items as obligatory. Participants will receive reminders for completing questionnaires by email up to three times. Participants allocated to the intervention group have unlimited access to the pDA during the study. Participants will not be restrained from using other information sources.

### Intervention

The online interactive pDA (named in Dutch ‘*Borstreconstructie Keuzehulp*’, translated in English as ‘Breast Reconstruction Decision Aid’) aims to support women in making a well-informed decision about breast reconstruction. It is developed to prepare women for consultation with a plastic surgeon. It contains evidence-based information about breast reconstructive options and their pros and cons. Furthermore, the pDA actively encourages women to weigh the options and discuss their preferences with their plastic surgeon during consultation.

The pDA consists of six modules: 1. Diagnosis, 2. Immediate breast reconstruction or not (yet)? 3. Expectations, 4. Considerations, 5. Patient stories, and 6. Summary (See Table 1 for a brief description of each module).

**Table 1 Tab1:** Overview and brief summary of the pDA’s modules

Module	Description of module
1. Diagnosis	Based on patient’s treatment options as provided to them by their clinician during the clinical encounter, patients tailor the pDA to their situation (i.e. whether or not the patient is eligible for nipple-sparing surgery, whether or not radiotherapy is or might be necessary following surgery, and whether or not the patient is eligible for BCS).
2. Immediate reconstruction or not (yet)?	Breast reconstruction options and their pros and cons are described. Options include undergoing immediate breast reconstruction, undergoing delayed breast reconstruction, and undergoing no breast reconstruction. Information is structured as answers to the following questions: ‘What choices do I have?’, ‘What are my options?’, ‘What are the pros and cons?’, ‘How much time do I have to think?’, ‘A period without a breast?’, ‘Sparing my skin and nipple?‘^a^, ‘When can I resume my normal activities?’, ‘When is breast reconstruction finished?’, ‘What is breast-conserving surgery?‘^b^
3. Expectations	Information about what patients can expect from undergoing breast reconstruction is provided. Also, the different types of breast reconstruction and their pros and cons are described. Options include implant-based breast reconstruction and autologous breast reconstruction. Information is structured as answers to the following questions: ‘What can I expect of a new breast?’, ‘What are the pros and cons of implant-based and autologous breast reconstruction?’, ‘What if I received breast radiation in the past?’, ‘What is implant-based breast reconstruction?’, ‘What is autologous breast reconstruction?’, ‘How will my breast look like?’, ‘How will my breast feel like?’, ‘Will this impact my body image?’, ‘What are potential complications?’, ‘What if I need breast radiation following surgery?‘^c^
4. Considerations	With value clarification exercises, women are actively encouraged to weigh the options of undergoing immediate breast reconstruction or not undergoing breast reconstruction (and potentially undergoing delayed breast reconstruction). Furthermore, women are invited to indicate their breast reconstruction preference and note questions they have for their plastic surgeon.
5. Patient stories	Short stories of six women who underwent breast surgery with or without breast reconstruction. The stories illustrate the experiences of these women with decision making about breast reconstruction and the impact of their decision on their daily life.
6. Summary	A summary sheet (A4 format), including patient’s personal considerations, preferences and questions for the plastic surgeon. The sheet can be saved as PDF and printed. Patients are encouraged to discuss the summary sheet with their plastic surgeon.

^a^Text of this section is rephrased dependent on whether or not patient is eligible for nipple-sparing surgery

^b^Only shown if the patient is eligible for BCS

^c^Only shown if radiotherapy is or might be needed

The information is tailored to patient’s treatment options relevant for decision making about breast reconstruction (i.e., whether or not the patient is eligible for nipple-sparing surgery, whether or not radiotherapy is or might be necessary following surgery, and whether or not the patient is eligible for BCS). Based on these treatment options, specific information is shown or text is rephrased (See Table 1 for details). Patients can further tailor the information to their needs by selecting the information that they want to read, in their own preferred speed and order. Information is presented in a balanced way, not favouring any particular outcome. The pDA also includes illustrations of different types of breast reconstruction. It takes approximately 60 min to complete the full program. The website is secured (https) and protected by a personal login code.

#### Development of the intervention

The pDA has been developed by clinicians and researchers of the Netherlands Cancer Institute (NKI), in partnership with ZorgKeuzeLab, a company specialized in the development and implementation of decision aids. The pDA was developed in close collaboration with a multidisciplinary working group consisting of 16 professionals from seven Dutch hospitals. Furthermore, an Australian psycho-oncology researcher and health psychologist (KS), developer of the breast reconstruction decision aid (‘BRECONDA’) [36, 40, 41], contributed as a consultant.

The pDA development was guided by the criteria of the International Patient Decision Aid Standards [42], and is in line with the Dutch guideline for the development of decision aids [43]. Furthermore, it was informed by a needs assessment among women who considered breast reconstruction following mastectomy in the past and healthcare professionals. Content was created by clinicians from the NKI based on most recent guidelines [13, 44], and was critically reviewed by members of the working group. The content was rewritten to B1 language level [45] (characterized by the use of common words and short, simple and active sentences) to be understandable for most people. The technical system was created based on the existing platform of ZorgKeuzeLab.

We tested the usability of the resulting pDA among women who considered breast reconstruction following mastectomy in thepast. Furthermore, healthcare professionals and representatives of the Dutch Breast Cancer Patient Organisation, who were not involved in the development, independently reviewed the pDA. Based on received feedback, minor adaptions were made to optimize the pDA. Detailed results of the developmental process will be published.

### Control group

Patients in the control group will receive a digital version of a widely available free information leaflet about breast reconstruction developed by the Dutch Cancer Society. This information leaflet is typically included in the standard breast reconstruction information materials in Dutch hospitals. The leaflet consists of 39 pages explaining all types of breast reconstruction including drawings and photos of results. In contrast to the pDA, the leaflet is not tailored to patient’s treatment options, does not contain value clarification exercises, patient stories and a summary sheet to discuss with a plastic surgeon, and it is not structured to guide decision making.

## Study measures

### Sociodemographic and clinical data

The patient’s age, country of birth, primary language, marital status, parity, education level, work status, internet experience, hereditary breast cancer risk, history of malignancy, surgery and/or radiotherapy of the breast, neo-adjuvant treatment, surgical risk factors (i.e. weight and height, smoking status, comorbidities), eligibility for BCS and/or nipple-sparing surgery, and indication for adjuvant radiotherapy will be obtained via the baseline questionnaire. Via postsurgical follow-up questionnaires (T2 and T3), we will obtain data on surgical treatment (including type and timing of breast reconstruction, if applicable), complications and adjuvant treatment. Surgical treatment and complications will be verified against data in the electronic medical record (EMR). Date of diagnosis, tumor characteristics, second malignancies and patient’s cup size will be collected from the EMR.

### Outcome measures

An overview of outcome measures, corresponding questionnaires and measurement time points is provided in Table 2.

**Table 2 Tab2:** Overview of outcome measures, corresponding instruments and measurement time points

Outcome measure	Instrument	Details	T0	T1	T2	T3
Decision-making process and decision quality						
Decisional conflict	Decisional Conflict Scale (DCS) [46, 47]	16 items, 5-point Likert-type scale, score range: 0–100, higher scores indicate more decisional conflict. Scores ≤25 are associated with follow-through decisions, and scores > 37.5 are associated with decision delay. Cronbach’s alpha = > 0.78 [47, 48]	x	x	x	x
Satisfaction with information	Three study-specific questions	How satisfied are you with the information about breast reconstruction? (5-point Likert-type scale: not at all – very satisfied), Did you miss information? (y/n), Would you have preferred less information? (y/n)			x	x
	Subscale Satisfaction with Information of the BREAST-Q [49] (slightly adapted), for women with breast reconstruction only	Satisfaction with information (Reconstruction module): 15 items, 4-point Likert-type scale, very unsatisfied – very satisfied, score range: 0–100, higher scores indicating higher satisfaction. Cronbach’s alpha = 0.94 [49]				
Satisfaction with plastic surgeon	Subscale Satisfaction with the Plastic Surgeon of the BREAST-Q [49]	Satisfaction with the Plastic Surgeon (Reconstruction module): 12 items, 4-point Likert-type scale, score range: 0–100, higher scores indicating higher satisfaction. Cronbach’s alpha = 0.97 [49]		x		
Preparedness for decision making	Preparation for Decision Making Scale [50, 51]	10 items, 5-point Likert-type scale, score range: 0–100, higher scores indicate higher perceived level of preparation for decision making. Cronbach’s alpha = 0.92–0.96 [51]		x		
Shared Decision Making	Shared Decision Making Questionnaire (SDM-Q-9) [52, 53]	9 items, 6-point Likert-type scale, score range: 0–100, higher scores indicate higher levels of perceived shared decision making. Cronbach’s alpha = 0.88 [53]		x		
Patient involvement in decision making	Control Preferences Scale [54]	1 item, 5-point Likert-type scale		x	x	
Knowledge of breast reconstruction	Study-specific questionnaire, translated and adapted from a questionnaire used in prior research [55]	10 items that can be answered with true/false/I don’t know. Items are about contraindications, risk factors, duration of the recovery period, impact of breast reconstruction on sensation, number of surgical procedures, complexity of types of breast reconstruction, complications, impact of breast reconstruction on breast cancer treatment and survival rates and the opportunity to spare the nipple. Total score is the number of correctly answered items, ranging from 0 to 10.	x	x	x	x
Decision regret	Decision Regret Scale (DRS) [56, 57]	5 items, 5-point Likert-type scale, score range: 0–100, higher scores indicating greater regret. Cronbach’s alpha = 0.81–0.92 [56]			x	x
Health outcomes						
Choice regarding breast reconstruction	Patient-reported questions and data from EMR				x	x
Satisfaction with breasts	Subscale Satisfaction with Breasts of the BREAST-Q Subscale Satisfaction with Breast Outcome of the BREAST-Q [49] (women with breast reconstruction only)	Satisfaction with Breasts (Reconstruction or Mastectomy Module, as appropriate): 16 items (women with breast reconstruction)/4 items (women without breast reconstruction)). Cronbach’s alpha = 0.96 (Reconstruction) [49]. Satisfaction with Breast Outcome (Reconstruction Module): 7 items, recall period: past 2 weeks. Higher scores indicate higher satisfaction. Cronbach’s alpha = 0.88 [49]			x	x
Body image	Subscale Body Image of the EORTC QLQ-BR23 [58]	4 items, 4-point Likert-type scale. Cronbach’s alpha = 0.69–0.91 [58]			x	x
Sexual functioning	Subscale Sexual Functioning of the EORTC QLQ-BR23 [58]	2 items + 1 item sexual enjoyment (if applicable), 4-point Likert-type scale. Cronbach’s alpha =0.87–0.94 [58]			x	X
Breast symptoms	Subscale Breast Symptoms of the EORTC QLQ-BR23 [58]	4 items, 4-point Likert-type scale. Cronbach’s alpha =0.46–0.85 [58]			x	X
Anxiety	STAI-6 (State scale of the State-Trait Anxiety Inventory) [59]	6 items, 4-point Likert-type scale,score range: 20–80, higher scores indicate higher levels of anxiety. Cronbach’s alpha = 0.82 [59]	x	x	x	x
Cost-effectiveness						
Use of health care services	A selection of questions of the Medical Consumption Questionnaire (see https://www.imta.nl/), and data from EMR	Selection of questions on the number of consultations related to breast surgery with a (plastic) surgeon, nurse practitioner/ nurse specialist, social worker, psychologist, general practitioner and a physiotherapist, and the amount of received home care during the last 3 months (T2) or 9 months (T3).			x	x
Health-Related Quality of life	EuroQoL-5D-5 L [60]	EuroQoL-5D-5 L descriptive system: 5 items, 5-point Likert-type scale, and the EQ Visual Analogue Scale: patients’ self-rated health.	x		x	x

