#### Costs

Unit costs will be estimated based on the trial data and published sources in the Netherlands [65]. Fixed costs of the development of the pDA will be based on the R&D of the pDA, including expected maintenance costs. For the control group, costs of a leaflet will be taken into account. Direct medical costs will include (1) treatment costs: type and number of (reconstructive) breast surgeries during study participation (data collected from the EMR), number of nights hospitalized (EMR)/inpatient days in hospital (for any reason) (EMR), and (2) resource use: participants are asked for professional care resources they used related to their breast (reconstructive) surgery. This consists of the number of consultations (live or by phone) with plastic surgeons and other medical and paramedical professionals pre- and post-operatively. For medical consumption, patients are asked to report on the received amount of home care (selection of items of the iMTA Medical Consumption Questionnaire on T2 3 months after surgery and T3 12 months after surgery; see https://www.imta.nl/). Production losses are measured by means of work status at T2 and T3, controlled for work status at baseline, and the number of hours in sick leave.

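### Table 2's recall windows for health-care use start at surgery, but the Costs section promises pre-operative consultations, and no source is named for that period

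*Protocol article*

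**What the plan says.** All references are to the protocol article.

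- **Table 2, row on use of health care services.** The row is marked at T2 and T3 only. It lists consultations related to breast surgery with several kinds of professional, among them the general practitioner, psychologist, social worker and physiotherapist. It then closes with "the amount of received home care during the last 3 months (T2) or 9 months (T3"). Its sources are a selection of Medical Consumption Questionnaire items and the EMR; it does not say which source supplies which item.
- **Procedure.** Follow-up is at "T1 (1 week after consultation with the plastic surgeon"), then "T2 (3 months after breast surgery) and T3 (12 months after breast surgery"). Randomisation follows consent and the baseline questionnaire and precedes the plastic-surgeon consultation.
- **Costs.** On resource use, "participants are asked for professional care resources they used related to their breast (reconstructive) surgery". This is said to consist of "the number of consultations (live or by phone) with plastic surgeons and other medical and paramedical professionals pre- and post-operatively". The EMR is named for surgeries, hospital nights and inpatient days. It is not named for consultations.
- **Intervention.** Of the decision aid: "It is developed to prepare women for consultation with a plastic surgeon".

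**The concern.** Two statements about the same cost item do not fit together. One section promises counts of consultations before and after surgery. The table that schedules the questions gives recall periods that, at the stated assessment times, reach back only to the operation.

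The stretch left uncovered runs from randomisation to surgery. In that stretch women receive the decision aid or the leaflet, see the plastic surgeon and decide. If the decision aid changes how many contacts a woman has before surgery, in either direction, the difference belongs in incremental cost. That quantity is the numerator of every ratio in the Cost-effectiveness analysis section and feeds the cost-effectiveness plane and the acceptability curve. Cost-effectiveness is the third stated aim of the trial.

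**Working it through.** **Inputs**

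| Input | Value | Where stated |
|---|---|---|
| T2 | 3 months after surgery | Procedure |
| T3 | 12 months after surgery | Procedure |
| Recall at T2 | 3 months | Table 2 |
| Recall at T3 | 9 months | Table 2 |
| Health-care-use items at T0 or T1 | none marked | Table 2 |

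**Step 1: when each window opens.** Start of window = assessment time − recall length, in months from surgery.

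- T2: 3 − 3 = 0, so the window is month 0 to month 3.
- T3: 12 − 9 = 3, so the window is month 3 to month 12.

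The windows join without gap or overlap and cover months 0 to 12 after surgery. Time before surgery covered: none. A T2 questionnaire completed late would open its window after surgery.

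**Step 2: coverage by source and period**

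| Contact | Randomisation to surgery | Months 0–12 after surgery |
|---|---|---|
| Hospital consultations, such as the plastic surgeon | No self-report window. The EMR could hold them, but no section assigns them to it | T2 and T3 self-report |
| General practitioner and other contacts outside the hospital | No self-report window and no other stated source | T2 and T3 self-report |
| Surgeries, hospital nights, inpatient days | EMR | EMR |

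That a hospital record may not hold outside contacts is an inference; the article does not say so.

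**Step 3: the other reading of the recall phrase.** Grammatically the 3- and 9-month limits could attach only to home care, the last item in the list. The consultation counts, which are asked at both T2 and T3, would then have no stated period. A woman could report the same visit twice, and whether pre-operative visits count would be left to her. The wording needs correction on this reading too.

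**Step 4: size.** Omitted incremental cost per woman = unit cost of a contact × difference between arms in mean pre-operative contacts. The article gives neither factor, so the product cannot be computed and its sign cannot be stated.

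**The case against.** The strongest reply is that the sections can be reconciled. The recall limit directly follows home care, and the Costs section also links the T2 and T3 questionnaire items to home care in a sentence separate from the one on consultations. Consultations may then be asked without a time limit, pre-operative ones included. Table 2 also names the EMR for this very row, and the Costs section never says that the EMR serves only surgeries and hospital stays. Finally, a journal article condenses the full protocol, and exact question wording is normally found there.

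Part of this stands. A reader might infer that pre-operative consultations are simply not captured. The documents do not support that: the EMR could supply the hospital contacts, and the scope of the recall phrase is ambiguous. A reader might also infer that consultations are what the decision aid is most likely to change. The article says only that it prepares women for a consultation, and every participant in either arm has already been referred to a plastic surgeon.

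What does not stand is that nothing needs changing. The home-care reading leaves the consultation counts without a period. Naming the EMR without saying which items it supplies does not assign consultations to it. And the point is not about detail left out: the article states both the windows and the promise of pre-operative counts, and as most naturally read they conflict.

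**Conclusion.** The conflict holds: as most naturally read, self-reported health-care use starts at surgery, while the Costs section says women are asked about consultations before it. The hospital part of the gap may be filled from the EMR, but the article does not say so. Contacts outside the hospital between randomisation and surgery have no stated source.

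The conclusion rests on two assumptions: that the recall limits govern the whole list of items, and that T2 is completed on schedule. If the first fails, the defect becomes an undefined recall period with possible double counting.

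The size is unknown. A reader might infer that the omission could reverse the sign of incremental cost. For illustration only, assume EUR 100–150 per contact and an arm difference of 0.25–0.5 contacts. The amount missed would be 0.25 × 100 = EUR 25 to 0.5 × 150 = EUR 75 per woman, or 25/20,000 = 0.00125 to 75/20,000 = 0.00375 QALY at the plan's threshold. None of these unit costs or contact differences is in the article, and it offers no expected incremental cost to compare them with, so a change of sign is not shown. Nor is bias shown: that needs a real gap and a non-zero difference between arms.

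The point should be settled before the economic analysis, because it concerns the numerator of each cost-effectiveness ratio. It does not touch the primary outcome or the validity of the randomised comparison.

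**What to change.** 1. Set the recall period for consultations at T2 to *since study entry (T0)*, and let T3 ask from T2 onward, so that the two periods join without overlap. State the period for home care separately.
2. Extract hospital consultations from randomisation to surgery from the EMR for all women in both arms, including those already past T2. Where a hospital visit appears in both sources, state which one is used.
3. Align Table 2 with the Costs section: give the source and period for each item.

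The cost is a somewhat longer recall at T2, with some loss of accuracy, and one more field in an EMR extraction that is already planned. For women already past T2, the EMR step can recover hospital contacts. Their outside contacts before surgery would remain unrecorded and should be reported as a limitation.
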